**Methods:**

A hybrid type 2 effectiveness implementation cluster randomised controlled trial will be implemented in the state of Goa, India. Twenty-eight clusters of villages and their associated public sector health centres will be randomly allocated through restricted randomisation. Clusters will be randomly allocated to the ‘Community Model’ or ‘Facility Model’ arms. All clusters will offer the HAP and clusters in the ‘Community Model’ arm will additionally receive activities delivered by community volunteers (“*Sangathis”*) to increase awareness about depression and support demand for and adherence to HAP. The primary outcomes are Contact Coverage (Patient Health Questionnaire [PHQ-9] score > 4 as a proportion of those screened) and Effectiveness Coverage (mean PHQ-9 score amongst those who score ≥ 15 at baseline, i.e. those who have moderately severe to severe depression) at 3 months post-recruitment. Additional outcomes at 3 and 6 months will assess sustained effectiveness, remission, response to treatment, depression awareness, social support, treatment completion, and activation levels. Economic and disability outcomes will be assessed to estimate incremental cost-effectiveness ratios. Implementation will be evaluated through process data and qualitative data informed by the RE-AIM framework. A minimum of 79488 primary care attenders will be screened for the Contact Coverage outcome, and 588 individuals with PHQ-9 ≥ 15 will be recruited for the Effectiveness Coverage outcome.

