### Objectives {7}

Through the IMPRESS (*IMP*lementation of evidence based facility and community interventions to reduce the treatment gap for dep*RESS*ion) programme, we aim to increase both the contact coverage and effective coverage of a scaled-up, evidence-based psychosocial treatment for depression (Healthy Activity Program-HAP) [9] and, in doing so, reduce the treatment gap for depression in a cost-effective manner. We will do this by examining if the addition of a community intervention (Community Model) delivered by community volunteers enhances the population-level impact of scaled-up HAP in routine primary care (Facility Model) by increasing demand for HAP and improving HAP adherence and effectiveness. We will conduct an economic evaluation, to estimate the cost-effectiveness of the Community Model in comparison to the Facility Model, and use the estimates of the cost of the delivery of the interventions to model the financial sustainability of scaling it up across India.

Our
*primary hypotheses* are that the Community Model will be superior to the Facility Model in reducing the treatment gap for depression through

(1a) Increasing the demand for depression treatment in primary care (contact coverage outcome); and(1b) Reducing depressive symptoms at three months post-recruitment amongst those who screen positive for moderately severe and severe depression (effectiveness outcome)

(2)Our *secondary hypotheses* are that the Community Model will be superior to the Facility Model in

(2a) Achieving a sustained reduction in symptoms of depression;(2b) Increasing short-term and sustained remission from depression;(2c) Achieving a greater response to HAP;(2d) Increasing perceived social support;(2e) Achieving higher treatment completion rates; and(2f) Increasing patient-reported activation levels.

In addition, we also hypothesize that the Community Model will increase community awareness about depression.

(3)Finally, we hypothesise that the superior outcomes of the Community Model will be mediated through:

(3a) Increased community awareness about depression (for contact coverage);(3b) Greater perceived social support (for effective coverage);(3c) Higher treatment completion rates (for effective coverage); and(3d) Increased patient-reported activation levels (for effective coverage).

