**Table 2 Tab2:** Outcome evaluation

**Outcome**	**Tool**	**Description**	**Population**	**Timeline**
*Primary*				
Contact coverage	PHQ-9	PHQ-9 score > 4 as a proportion of those screened	Adult health centre attenders	Until we achieve target sample size
Effectiveness coverage	PHQ-9	Mean PHQ-9 score	Individuals who consent to receive HAP	3 months post recruitment
*Secondary*				
Sustained effectiveness	PHQ-9	Mean PHQ-9 score	Individuals who receive HAP	6 months post recruitment
Remission	PHQ-9	PHQ-9 score < 10	Individuals who receive HAP	3 and 6 months post recruitment
Response to treatment	PHQ-9	> 50% reduction in PHQ-9 score	Individuals who receive HAP	3 and 6 months post recruitment
Cost-effectiveness	(1) Inventory form for collecting system-level economic costs of delivering interventions (2a) Client Service Receipt Inventory form for collecting costs to patients (2b) Survey form for collecting costs of receiving HAP intervention to patients (3) WHODAS	(1) System-level costs: economic costs in WHO six building blocks for delivering the interventions (2a) Out-of-pocket costs for receiving general medical care and the related non-medical costs (e.g. time loss, travel) (2b) Out-of-pocket costs for receiving HAP intervention (e.g. time loss, travel) (3) Standardised disability scores used to estimate QALYs	(1) Finance records and individuals involved in delivery of the interventions (2a) Individuals who receive HAP (2b) Individuals who receive HAP (3) Individuals who receive HAP	(1) System-level costs: monthly, during the period of implementation (2a) Patient-level costs: 3 and 6 months post recruitment (2b) Patient level costs: 3 months post recruitment (3) 3 and 6 months post recruitment
Depression Awareness Questionnaire	Bespoke tool	Awareness about depression	Adult health centre attenders	Baseline and on randomly selected days at 6 and 12 months of implementation
Perceived social support	MSPSS	Perception of social support received	Individuals who receive HAP	3 and 6 months post-recruitment
	Bespoke tool			3 and 6 months post-recruitment
Treatment completion	Process data	Met treatment goals or completed the maximum number of sessions or were referred to mental health specialists	Individuals who receive HAP	Across the 12 months of implementation
Behavioural activation	PREMIUM Abbreviated Activation Scale	Patient-report activation levels	Individuals who receive HAP	3 and 6 months post-recruitment

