#### Qualitative data

These will include data collected using in-depth interviews (IDIs) and focused group discussions (FGDs) with various stakeholders involved in delivering the interventions, individuals with depression, and decision makers and implementors at various levels in the health system as outlined in Table 3.

**Table 3 Tab3:** Implementation monitoring and evaluation

**Indicator**	**Source**	**When**	**RE-AIM Dimension**^a^
*Patient level*			
Number of HAP patients who were followed up in the community	Process data from *Sangathi* registers	During implementation	R
% eligible for HAP who receive at least one session of HAP (uptake)	Process data from screening register, PEERS app	During implementation	I
% treatment completers	Process data from PEERS app	During implementation	I
Adherence to homework	Process data from PEERS app	During implementation	I
Acceptability of community intervention	In-depth interviews (IDIs) with individuals receiving the intervention	After completion of 6-month outcome evaluation	R
Number of people with possible depression referred by *Sangathis*	Process data from *Sangathi* registers	During implementation	R
*Counsellor level*			
Characteristics of counsellors who agreed to join the programme	Process data from training register	During training	A
Knowledge	Multiple Choice Questionnaire administered to HAP counsellors	Pre- and post-training	I
Acceptability of training	Focused group discussions (FGD) with counsellors and HAP facilitators	Post-training	A
Fidelity of training	Direct observation of HAP facilitators	During training	I
Skill- based competency	ENACT tool to rate skills of HAP counsellors	Pre- and post-internship	I
Therapy quality	PEERS app	During implementation	I
Acceptability of supervision	IDIs/FGDs with counsellors and HAP facilitators	During implementation	A
Number/duration of supervision sessions attended (feasibility)	PEERS app	During implementation	I
Acceptability of HAP	IDIs/FGDs with counsellors	During implementation	A
Fidelity	Audio recording of HAP sessions	10% of audio-recordings by independent evaluators	I
Perceived benefits and barriers of implementing and sustaining programme	IDIs/FGDs with counsellors	During implementation	A
*Sangathi level*			
Characteristics of *Sangathis* who agreed to join the programme	Process data from recruitment register	During training	A
Acceptability of training	IDIs/FGDs with *Sangathis* and *Sangathi* facilitators	Post-training	A

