### Participant timeline {13} (Table 4)

**Table 4 Tab4:**
[figure not shown]
Schedule of enrolment, interventions, and assessments

Participants will be identified and recruited by the trained and supervised case managers at the health centres. Health centre attenders meeting the eligibility criteria will be screened using the PHQ-9 questionnaire [29], a nine-item questionnaire that has been validated and extensively used in the study setting [15, 30]. Participants who score > 4 (mild depression and above) will contribute to the contact coverage outcome.

Due to the limited caseload capacity of the counsellors, we will prioritise HAP for the most severely unwell, who have also been shown to derive the greatest benefit from such interventions [31]. This means that only those who score ≥ 15 (moderately severe to severe depression) will be eligible to receive the HAP intervention and will contribute to the effectiveness coverage outcome. After consent has been obtained from those eligible for the effectiveness coverage component, the case manager will collect the data on the following potential effect-moderators: age, gender, marital status, education and employment status; and other outcomes: WHODAS 2.0, MSPSS, and PAAS. All assessments will be audio-taped (with consent), and the tapes will be randomly selected for review by the supervisor for quality assurance. The outcomes will be measured at 3 and 6 months post recruitment. The qualitative data with trial participants will be collected after the 6-months outcome evaluation. The process data will be collected at various timepoints during the implementation as outlined in Table 3.

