### Sample size {14}

#### Contact coverage outcome

We will screen for 5 days a week for 12 months (52 weeks) in all 30 health centres. Based on screening numbers over the first two months of the trial (average of 6624 per month), we will be able to screen 79,488 over 12 months. Based on the screening data from the first 2 months of the IMPRESS trial, the prevalence of depression (PHQ-9 score > 4) amongst those screened at the health centres is 14%. Assuming this prevalence in health centres in the Community Model, this sample size provides 86% power to detect a difference with a prevalence of 11% in those screened at the health centres in the Facility Model at the 5% significance level, assuming a coefficient of variation of 0.2 as below.

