#### Contact coverage

The primary analyses will compare the proportion of individuals identified with depression through screening in the health centres. Logistic regression will be used to compare the number of individuals between arms, allowing for within-facility clustering. We will also do a sensitivity analysis to examine the contact coverage for moderate depression and above (i.e. PHQ9 ≥ 9).

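### A PHQ-9 score of 9 counts as moderate depression in the contact-coverage sensitivity analysis and as remission in Table 2; the two cut-offs should be reconciled before analysis

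*Protocol article*

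**What the plan says.** The protocol article uses four PHQ-9 thresholds.

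- **Primary contact coverage** (Participant timeline {13}; also Outcomes {12} and Table 2): "Participants who score > 4 (mild depression and above) will contribute to the contact coverage outcome".
- **Contact-coverage sensitivity analysis** (Statistical methods {20a}, Contact coverage): the investigators will "examine the contact coverage for moderate depression and above (i.e. PHQ9 ≥ 9").
- **Remission** (Table 2, a secondary outcome at 3 and 6 months in people who receive HAP): "PHQ-9 score < 10".
- **Eligibility for HAP and for the effectiveness outcome** (Participant timeline {13}): "only those who score ≥ 15 (moderately severe to severe depression) will be eligible to receive the HAP intervention".

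Objectives {7} states hypothesis 1a as "Increasing the demand for depression treatment in primary care (contact coverage outcome"), and the same section speaks of increasing demand for HAP.

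**The concern.** Two labels on one scale overlap. An attender who scores 9 at screening would be counted with moderate depression and above, while a treated participant who scores 9 at follow-up would be counted as remitted. The protocol gives no other numerical lower bound for moderate, so the remission cut-off is the only internal comparator, and 9 does not fit it.

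This matters because it is the only alternative threshold stated for a primary outcome. In a distribution that falls with severity, the lowest score admitted holds a sizeable part of the group, so a shift of one point changes who is being compared. If the overlap is noticed only after the data have been seen, correcting it becomes a post hoc change of threshold.

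A second, lesser matter is fit to the aim. Both stated contact-coverage thresholds admit people who score below 15 and so are not offered HAP. A rise confined to lower scorers would appear in both results, and neither would show whether more HAP-eligible people had presented.

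**Working it through.** **1. The plan's own figure, and whether the cut-off enters it.** Sample size {14} gives 86% power for 14% against 11%, a coefficient of variation k of 0.2 and 5% significance (two-sided assumed), on the statement that "we will be able to screen 79,488 over 12 months". The standard formula for an unmatched cluster trial is

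power = Φ( √[ C(p1 − p2)² / V ] − 1.96 ), with V = [p1(1 − p1) + p2(1 − p2)]/m + k²(p1² + p2²),

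where C is the number of clusters per arm, or one fewer with the small-sample correction.

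- 28 clusters: m = 79,488/28 = 2,839; V = 0.2183/2,839 + 0.04 × 0.0317 = 0.000077 + 0.001268 = 0.001345. C = 14 gives Φ(3.061 − 1.96) = 86.5%; C = 13 gives Φ(2.949 − 1.96) = 83.9%.
- 30 centres: m = 2,650. C = 15 gives 88.5%; C = 14 gives 86.3%.

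The stated 86% is reproduced under two of these four variants. It rests on the proportion scoring above 4. The cut-off of 9 appears nowhere in it.

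**2. The overlap.**

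| Definition | Scores included |
|---|---|
| Sensitivity analysis, ≥ 9 | 9 to 27 |
| Remission, < 10 | 0 to 9 |
| Scores in both | 9 |
| Scores in both if the sensitivity cut-off were ≥ 10 | none |

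**3. How much of the group is at stake.** The protocol gives no score distribution, so this step is an assumption shown with a range. Let the proportion scoring at least s fall by a constant factor q per point, from 14% at 5 to a proportion T at 15. Then q = (T/0.14)^(1/10), the share of the ≥ 9 group scoring exactly 9 is 1 − q, and the ratio of the ≥ 9 group to the ≥ 10 group is 1/q.

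The low end of T is 588/79,488 = 0.74%. That 588 is a recruitment quota (21 × 28), not a prevalence, so T could well be higher. The other rows use twice and three times that value.

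| T (≥ 15) | q | Share at exactly 9 | Ratio ≥ 9 to ≥ 10 |
|---|---|---|---|
| 0.74% | 0.745 | 25% | 1.34 |
| 1.48% | 0.799 | 20% | 1.25 |
| 2.22% | 0.832 | 17% | 1.20 |

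The proportion of attenders counted, 0.14q⁴ at ≥ 9 and 0.14q⁵ at ≥ 10, would be 4.3% against 3.2% in the first row and 6.7% against 5.6% in the last. Within this model 25% is the upper end.

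**4. Precision of an optional analysis at ≥ 15.** Keeping k = 0.2 and m = 2,839, the relative variance of one arm's proportion is proportional to (1 − p)/(mp) + k². At 14% this is 0.0022 + 0.04 = 0.0422. At 0.74% it is 0.0472 + 0.04 = 0.0872, and at 2.22% it is 0.0155 + 0.04 = 0.0555. The relative standard error would therefore be about √(0.0555/0.0422) = 1.15 to √(0.0872/0.0422) = 1.44 times that of the primary comparison. The analysis is less precise but usable.

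**The case against.** The best case for leaving the text alone is that remission and moderate depression serve different purposes. Remission is a follow-up outcome in people who entered at 15 or more; the figure of 9 defines a category among screened attenders. One need not be the exact complement of the other. This stands in part: a reader might infer that the documents prove 9 to be the wrong number, or that attenders scoring 9 are mild cases, and they show neither. They show an overlap on one scale, with nothing supporting 9. A slip for > 9 is plausible, since the primary threshold is written as > 4, but that is inference.

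A reader might also infer that no analysis uses the HAP-eligible group. That is wrong. The second primary outcome is the "mean PHQ-9 score amongst those who score ≥ 15 at baseline", and Table 3 reports the percentage "eligible for HAP who receive at least one session of HAP (uptake"). The statement is true only of contact coverage. Neither of those quantities shows whether more eligible people presented, because recruitment is fixed at 21 per cluster and uptake is conditional on eligibility.

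Nor is the lack of a contact-coverage analysis at 15 or more an error. Contact coverage is set consistently at > 4, the HAP threshold is a stated decision based on counsellor capacity, and contact below 15 can still lead to other care through referral or a medical officer's prescription. A detailed analysis plan is to be agreed before any analysis and may already contain this run.

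**Conclusion.** The inconsistency is real and small. One score, 9, carries two incompatible labels, and the lower bound given for moderate has no support elsewhere in the protocol. The consequence is limited to one sensitivity analysis, for which no power is claimed, of a primary outcome. Primary contact coverage, the sample sizes and the 86% power are untouched.

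The affected share, 17% to 25% of the ≥ 9 group, rests wholly on the geometric tail and on the assumed range of 0.74% to about 2.2% scoring 15 or more; the observed screening data could give a different value. The analysis at 15 or more is a suggested improvement, not a correction.

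**What to change.** Before any analysis, set the sensitivity cut-off for moderate depression and above at PHQ-9 ≥ 10 (that is, > 9), and carry the same number into the analysis plan. This is the smaller change: moving the remission boundary instead would alter a secondary outcome at two time points. If 9 was intended, the protocol should give its basis and say why it differs from the remission boundary. The cost is one corrected number; the PHQ-9 is already collected at screening.

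Optionally, prespecify the same contact-coverage model at PHQ-9 ≥ 15, labelled as a secondary comparison. This would show directly whether the Community Model brings in more people who can be offered HAP. The cost is one further run on existing data, with the lower precision shown above.

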#### Effectiveness coverage

The primary analyses will be intention-to-treat. Linear regression GEE will be used to compare mean PHQ-9 scores by arms, adjusting for within-facility clustering, baseline severity of depression and any confounding factors for which there is substantial imbalance between the arms at baseline. We will present an estimate of the effect size as an adjusted SMD and 95% confidence intervals and the intra-cluster correlation. For binary outcomes, the effect will be measured by the risk ratio (RR) and 95% confidence intervals using logistic regression models adjusted for within-facility clustering. Predefined effect-modification analyses will include adjustment for age, gender, marital status, education, employment status, and baseline PHQ-9 score. Finally, we will consider a sensitivity analysis to investigate the effect of missing data by using multiple imputation. We will not conduct an interim analysis as we do not anticipate any safety concerns related to the interventions.

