## Assignment of interventions: allocation

### Sequence generation {16a}

The allocation sequence was generated through restricted randomisation using the following parameters: (a) type of health centre (PHC, CHC, SDH) associated with the cluster; (b) availability of DMHP services in the health centre; and (c) population size of the cluster. A randomly selected seed number was used to enable the randomisation procedure to be reproduced. The randomisation was done before the start of the trial as both the embedding of the trial and other implementation processes (e.g. training of community intervention delivery agents) had to be initiated in advance of recruitment of the first participant.

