## Statistical methods

### Statistical methods for primary and secondary outcomes {20a}

A detailed analysis plan will be agreed with the data safety and monitoring board towards the end of the trial and before any analysis is undertaken. Findings will be reported as per the CONSORT guidelines for CRTs. Baseline comparability will be assessed for participants who could and could not complete outcome assessments. Comparability of the two intervention arms will be assessed for potential confounding factors such as age, gender, education, and severity of depression at baseline.

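### Extra covariates in the primary PHQ-9 model are chosen by observed imbalance, with no threshold; this rule will rarely pick the restricted-randomisation factors, which neither stated primary model includes

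*Protocol article*

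**What the plan says.** All references are to the protocol article.

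- **Effectiveness coverage (statistical methods).** "Linear regression GEE will be used to compare mean PHQ-9 scores by arms, adjusting for within-facility clustering, baseline severity of depression" and, beyond that, "any confounding factors for which there is substantial imbalance between the arms at baseline". Baseline severity is therefore fixed in advance; the remaining covariates are not.
- **Statistical methods {20a}, opening paragraph.** "Comparability of the two intervention arms will be assessed for potential confounding factors such as age, gender, education, and severity of depression at baseline". The list is illustrative, not closed, and names no cluster-level factor. The same paragraph promises a detailed analysis plan late in the trial, before any analysis.
- **Contact coverage (statistical methods).** "Logistic regression will be used to compare the number of individuals between arms, allowing for within-facility clustering". No covariate is named and there is no imbalance rule.
- **Sequence generation {16a}.** "The allocation sequence was generated through restricted randomisation using the following parameters": health-centre type (three levels), availability of DMHP services, and cluster population size. None of the three appears in either primary model or in the list of potential confounders.

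**The concern.** Two things follow from the rule as written.

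First, the covariate set of a primary model is unknown until the arms have been compared. With no threshold and an open list, two statisticians following the text could fit different primary models to the same data. Case managers enrol participants, know the allocation, and recruit after clusters were randomised (Implementation {16c}, Who will be blinded {17a}, Sequence generation {16a}). Imbalance in participant characteristics may therefore be systematic, which makes it more important to name the participant-level covariates in advance.

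Second, an imbalance rule points away from the covariates that the design makes relevant. Restriction keeps the three factors similar between arms, so they will seldom look imbalanced. Any variance that they explain has been removed from the arm comparison but, without adjustment, stays in the standard error. The result is an interval that is too wide and some power given away, in a trial with only 28 clusters.

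**Working it through.** **1. The stated PHQ-9 power reproduces.** Inputs from Sample size {14}: 14 clusters per arm, m = 17 analysed per cluster, means 11.9 and 8.9, SDs 7.0 and 7.2, coefficient of variation k = 0.2, alpha 5% (taken as two-sided). The Hayes–Bennett formula is

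c = 1 + (1.96 + 0.84)² × [(7.0² + 7.2²)/17 + 0.2² × (11.9² + 8.9²)] / 3.0² = 13.88,

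so 14 clusters per arm. Power at 14 is 80.4%, against 80% stated. The sample size is not in question.

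**2. Data dependence of the covariate set.** The threshold is an assumption, because the protocol gives none. With 14 × 17 = 238 analysed per arm, a standardised baseline difference has standard error √(2 × D/238). The design effect D is 1 without clustering, or 1 + 16 × 0.05 = 1.8 at an assumed covariate ICC of 0.05. That gives 0.092 or 0.123. The chance that at least one of age, gender and education passes the threshold, treating them as independent, is 1 − (1 − p)³:

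| Threshold | D = 1 | D = 1.8 |
|---|---|---|
| 0.10 | 62% | 80% |
| 0.20 | 8–9% | 28% |
| 0.25 | 2% | 12% |

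These are chance imbalances only. Computed on all recruited participants they would be somewhat lower. The main message is the spread: whether the model gains covariates depends largely on a number that the plan does not state.

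**3. Why the restriction factors are missed.** If restriction holds a factor within, say, 0.1 SD between arms (an assumption), a rule with a threshold of 0.1 or more cannot select it.

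**4. Effect of leaving them out on type I error.** A cluster-level simulation of the PHQ-9 outcome (28 clusters, restricted allocation, 6,000 runs per setting) gave, for assumed shares of between-cluster variance explained of 0, 10, 30 and 50%, a type I error of 5.3, 4.1, 3.0 and 2.4% without adjustment. With adjustment it was about 5% throughout. The omission is conservative.

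**5. Effect on power.** Let R be the share of between-cluster variance explained. The variance of a cluster mean is v = σb²(1 − R) + σw²/m, and SE = √(2v/14). Power comes from the noncentral t with 26 df unadjusted, or 23 df with three covariate terms.

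- *PHQ-9:* σb² = 0.04 × (11.9² + 8.9²)/2 = 4.416; σw²/m = 50.42/17 = 2.966; SE = 1.027; noncentrality 3.0/1.027 = 2.92; unadjusted power 80.3%.
- *Contact coverage, 11% versus 14%:* m = 79,488/28 = 2,839; σb² = 0.04 × (0.14² + 0.11²)/2 = 0.000634; within part = 0.1092/2,839 = 0.0000384; SE = 0.0098; noncentrality 3.06; unadjusted power 83.8%. Between-cluster variation is 0.000634/0.000672 = 94% of the variance of a cluster proportion, so more screening hardly helps.

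| R (assumed) | PHQ-9 | Contact coverage |
|---|---|---|
| unadjusted | 80.3% | 83.8% |
| 0 | 79.9% | 83.4% |
| 10% | 82.3% | 86.9% |
| 20% | 84.6% | 90.2% |
| 30% | 87.0% | 93.3% |

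The 86% stated for contact coverage is recovered at 86.3% with 15 clusters per arm, or at 86.5% with 14 per arm and no small-sample term. The 83.8% here uses the 28 randomised clusters and a t reference, as a common base for the comparison.

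The unadjusted row treats allocation as unrestricted. Restriction itself gives an unadjusted analysis a little back: in the PHQ-9 simulation, power without and with adjustment was 80.9% and 82.3% at R = 10%, and 81.6% and 86.8% at R = 30%. The true gain is thus slightly smaller than the table suggests.

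**The case against.** The strongest reply is that this is a condensed article, that a detailed analysis plan is promised before any analysis, and that naming randomisation factors as covariates is ordinary content for that plan. This stands in part. The models as stated do not include the factors; that is not the same as a decision to exclude them, and silence alone would not be a finding. But on the PHQ-9 covariates the article is not silent. It commits the primary model to a selection rule, and a plan faithful to it inherits that rule.

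It can also be said that selection uses baseline data and not outcomes, that the trial statistician is blinded to arm, and that baseline severity, plausibly the strongest covariate, is already fixed. All true. They limit the harm of data dependence to the additional covariates; they do not supply a threshold or a list.

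The power gain rests on an assumed R. That is correct: nothing in the document says that the factors explain anything, so the range has to start at zero.

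A reader might infer more than the document supports. It does not show that leaving out the restriction factors biases the estimate or raises the false-positive rate; the check shows the reverse. Nor is the contact-coverage model data-dependent: it carries no imbalance rule, and its only issue here is that the restriction factors are absent.

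**Conclusion.** The point holds as a correctable weakness, not a threat to validity. The PHQ-9 model's covariates beyond baseline severity are not fixed, and under plausible thresholds the chance of adding at least one of three named candidates runs from 2% to 80%. The restriction factors are absent from both stated primary models, and the imbalance rule would rarely bring them in. The consequence is conservative inference and possible loss of power. With 3 df spent and 0–30% of between-cluster variance explained, adjustment changes power by −0.4 to +6.7 points for PHQ-9 and by −0.4 to +9.5 points for contact coverage. Those figures depend on the assumed R, on k = 0.2 as stated, and on a two-sided 5% test; the thresholds and the covariate ICC of 0.05 are also assumptions.

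**What to change.** Before any analysis, replace the imbalance rule in the primary PHQ-9 model with a closed covariate list:

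- **Both primary models:** health-centre type, DMHP availability and cluster population (for example on a log scale), coded sparingly for 28 clusters. With 20 primary health centres, six community health centres and two sub-district hospitals, a two-level type variable spends 3 df in total. Keeping three levels spends a fourth and gives PHQ-9 power of 79.7% if the factors explain nothing.
- **PHQ-9 model:** in addition, continuous baseline PHQ-9, age, gender and education. The last three are the characteristics that the article already names for its comparability check.
- **Sensitivity analysis:** keep imbalance-based adjustment here, with a stated threshold and candidate list, so that any systematic imbalance from post-allocation recruitment is still examined.
- **Reporting:** show the result without these added covariates alongside.

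The cost is wording. The restriction factors were used at randomisation and the participant covariates are collected at recruitment (Participant timeline {13}), so no new data are needed. The statistical price is about 3 of 26 cluster-level degrees of freedom, at most about 0.4 points of power if the factors explain nothing.
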